### Outcomes

The antibiotics protocol guided by LUS and PCT will be considered an improvement in the quality of care if a reduction in the prescription of antibiotics is observed, and also if there is a reduction in the number of days on antibiotics. Another primary outcome will be the increase in the sensitivity and specificity when diagnosing bacterial pneumonia using LUS. Secondary outcomes will be the reduction of the irradiation dose using the new protocol (with a reduction in economic costs as well), and a high LUS interobserver agreement.

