### Inclusion and exclusion criteria

Inclusion: Children under 18 years old with suspected community pneumonia who require admission to the PICU or patients with suspected nosocomial pneumonia during their PICU stay.

Exclusion: Patients with underlying pathologies such as cystic fibrosis or who are immunocompromised. Patients who develop nosocomial pneumonia after being included in the study due to community pneumonia. Patients who have a CXR taken before being admitted to the PICU.

Withdrawal and abandonment criteria: Violation of study protocol, withdrawal of parental consent, death.

Patients withdrawing or with loss of protocol adherence will be excluded from the study.

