### Sample size

Sample size calculations will be performed using the statistical program Ene 2.0®. The main variable will be the existence of differences between CXR and LUS in patients with community pneumonia and nosocomial pneumonia. H1 will be considered as the existence of differences between LUS and CXR. An 80% power will be required to detect differences in the contrast of the null hypothesis H0: p1 = p2, using a bilateral X^2^ test for two independent samples. If we consider a significance level of 5%, it will be necessary to include 63 units in the control group and 63 units in the experimental group. A total of 126 patients will be included for community pneumonia. Twenty-eight patients per group will be included for nosocomial pneumonia; therefore, there will be 56 patients in total for this kind of pneumonia. After 12 months of recruitment, a preliminary analysis will be carried out to guarantee the safety of the patients. Respiratory infection represents around 30–70% of the PICU admissions, depending on the season. There will be an estimated 200–300 recruitable patients per year, so it is expected that the calculated sample size will be attainable.

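### Improved quality of care is declared from lower antibiotic use with no condition on clinical outcome, while children who die are excluded from the study

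*Protocol article*

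**What the plan says.** All references are to the protocol article.

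- **Outcomes.** The LUS-and-PCT-guided antibiotic protocol "will be considered an improvement in the quality of care if a reduction in the prescription of antibiotics is observed". A shorter duration of antibiotic treatment is named as a second sign of improvement. The section continues: "Another primary outcome will be the increase in the sensitivity and specificity when diagnosing bacterial pneumonia using LUS". The secondary outcomes are irradiation dose, cost and interobserver agreement on LUS. Death, respiratory support, length of PICU stay and late start of antibiotics are not named.
- **Inclusion and exclusion criteria.** "Withdrawal and abandonment criteria: Violation of study protocol, withdrawal of parental consent, death". The consequence is stated next: "Patients withdrawing or with loss of protocol adherence will be excluded from the study".
- **Statistical analysis.** A child who is randomised but does not complete the treatment is not analysed.
- **Methodology.** In both arms, PCT below 1 ng/mL with an image not suggestive of bacterial pneumonia leads to no antibiotic. The arms differ in the image used (LUS or chest X-ray, CXR).
- **Sample size.** 63 per group for community and 28 per group for nosocomial pneumonia. On safety: "After 12 months of recruitment, a preliminary analysis will be carried out to guarantee the safety of the patients". On accrual: "There will be an estimated 200–300 recruitable patients per year".

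**The concern.** The primary goal is better quality of care. The Background takes this to mean correct diagnosis and treatment with as little exposure to harm as possible, and the Discussion repeats the part on correct diagnosis and treatment. The stated rule tests only one side of that. Antibiotic use falls when unnecessary courses are avoided, and it also falls when true bacterial pneumonia is missed; the rule does not separate the two. The children who would show the difference are those most likely to leave the data: a child who dies is withdrawn and excluded, and a child who does not complete treatment is not analysed. A child given antibiotics after a no-antibiotic classification might also be read as a protocol violation and excluded, although the article does not say so.

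At stake is the headline conclusion. The trial could report better care for critically ill children on evidence that shows only lower antibiotic use in those who survived and adhered to the protocol.

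**Working it through.** **1. The passages side by side.** The quality claim has two inputs, prescriptions and days. Sensitivity and specificity come in a separate sentence as another primary outcome, with no wording that links them to the claim. Since death leads to exclusion, deaths cannot appear in either arm of the analysed set. A comparison of mortality is therefore empty by construction, and the antibiotic comparison is restricted to survivors.

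**2. Can the rule move in the wrong direction?** Let π be the bacterial share, and Se and Sp the sensitivity and specificity of the whole antibiotic decision (image plus PCT).

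- Proportion prescribed = π·Se + (1 − π)(1 − Sp)
- Untreated bacterial cases per arm = 91·π·(1 − Se), with 63 + 28 = 91 children per arm

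The Background gives a viral share of 60–70%, so π = 0.30–0.40 if the remainder is taken as bacterial. Sp = 0.60 in both arms and Se = 0.90 against 0.70 are assumptions; the article gives no such values.

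| π | Prescribed, Se 0.90 | Prescribed, Se 0.70 | Untreated bacterial, Se 0.90 | Untreated bacterial, Se 0.70 |
|---|---|---|---|---|
| 0.30 | 0.27 + 0.28 = 55% | 0.21 + 0.28 = 49% | 91 × 0.03 = 2.7 | 91 × 0.09 = 8.2 |
| 0.40 | 0.36 + 0.24 = 60% | 0.28 + 0.24 = 52% | 91 × 0.04 = 3.6 | 91 × 0.12 = 10.9 |

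The fall in prescribing is π × 0.20, that is 6 or 8 points. It equals the rise in untreated bacterial cases: 91 × 0.06 = 5.5 and 91 × 0.08 = 7.3 children. Two limits apply. The calculation treats missed cases as never treated; if they are treated later and those courses count, the fall shrinks. And with 91 per arm the power to find such a fall significant is only 12% (55% vs 49%) or 19% (60% vs 52%). The table shows the direction of the rule, not how likely a false claim is.

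**3. What can 182 children say about harm?** The total is 126 + 56 = 182. Event rates are assumed, with both strata pooled.

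- Half-width of the 95% interval for a risk difference, equal rates p: 1.96 × √(2p(1 − p)/91). For p = 0.05 this is 1.96 × 0.0323 = 6.3 points; for p = 0.10 it is 1.96 × 0.0445 = 8.7 points.
- Power at two-sided 5%: 25% for 5% vs 10%, 40% for 3% vs 9%, 62% for 5% vs 15%.
- Number per group to rule out an excess m at one-sided 2.5% and 80% power: (1.96 + 0.84)² × 2p(1 − p)/m². For m = 10 points this gives 75, 142 or 201 at p = 5%, 10% or 15%. For m = 5 points it gives 299, 566 or 801.

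With 91 per group, only the 10-point margin at a 5% base rate is within reach.

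**4. Timing of the safety look.** If every recruitable child enrolled, 182 would be reached in 182/300 × 12 = 7.3 to 182/200 × 12 = 10.9 months. September 2017 to December 2019 is 4 + 12 + 12 = 28 months; even accrual over that period puts 182 × 12/28 = 78 children (43%) in the trial at 12 months.

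**The case against.** The strongest objection is that missed infection is measured. Sensitivity for bacterial pneumonia is a primary outcome and a main objective, and a test that missed many bacterial cases should score badly on it. This stands in part: a reader might infer that the plan has no means of seeing under-treatment, and that goes too far. But the quality claim is not conditional on that outcome. The protection is also incomplete: the article states no separate reference standard, and its definition of community pneumonia uses the imaging itself with C-reactive protein or PCT. A LUS-negative, low-PCT child still meets that definition if a CXR was taken and was positive and C-reactive protein was raised, but not otherwise.

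Second, antibiotics started later add to both prescriptions and days, so a missed case treated late is not simply a gain. This stands. It is why under-treatment could be counted as improvement, not that it would be.

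Third, both arms follow the same PCT-plus-image rule and the control arm is described as current unit protocol. The contrast is LUS against CXR, not withholding against treating. This also stands, but a difference in missed cases between the two images is exactly what the rule cannot separate from better targeting.

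Fourth, a reader might infer that the safety look has nothing to examine, or is the only monitoring. The documents do not support that: a condensed article may leave the variables and any further monitoring to the full protocol. Nor do they support saying that enrolment will finish before the look. The 7.3 to 10.9 months treats a pool of recruitable children as fully enrolled and is only a fastest-case bound.

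**Conclusion.** The point holds in this form: the stated criterion for better quality of care rests on antibiotic use alone, no clinical outcome is listed beside it, and the exclusion rules remove deaths and non-completers from the comparison. A fall in prescribing due to missed bacterial pneumonia could therefore be counted as improvement. This rests on the article's explicit wording of the rule and the exclusions, not on detail it leaves out.

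The size is illustrative: 6 to 8 points of apparent improvement, and 5.5 to 7.3 more untreated bacterial cases per 91 children, under the assumed sensitivity, specificity and bacterial share, with no late treatment. The chance of this happening cannot be derived from the documents. The timing of the safety look is a minor matter; about 78 of 182 children at 12 months is the more plausible figure given the stated study period.

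**What to change.** - **Population.** Remove death and protocol violation as grounds for exclusion, drop the rule that non-completers are not analysed, and analyse all randomised children in their assigned arm with deaths counted as events.
- **Outcomes to report by arm, with 95% confidence intervals.** Death and escalation of respiratory support as events; PICU days separately, because they are not an event; and antibiotic start after an initial no-antibiotic classification, with all randomised children as denominator. Describe the last as a consequence of the algorithm and keep it out of any composite: it can occur only in children first left untreated, so an arm that correctly withholds more has more children at risk of it.
- **Claim.** State in the Outcomes section that improved quality of care is claimed only if antibiotic use falls and the interval for clinical harm excludes a worsening stated in advance. Otherwise claim only fewer antibiotics.
- **Minor.** Tie the safety look to a number randomised instead of 12 calendar months. The article describes recruitment in the past tense, so this may no longer be possible; the other changes affect only analysis and reporting.

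The cost is wording and data that routine PICU records should already hold. The downside is a more modest conclusion: with 91 per arm the harm interval spans roughly 6 to 9 points either side at assumed rates of 5–10%, so the narrower claim is the likely result.

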### Data collection

The study coordinator will register patients, verifying compliance with all the inclusion criteria. An external company will be appointed to monitor the study and ensure compliance with correct clinical practice principles (ICHE6). Once the notebooks are audited, they will be entered into a validated database, one with restricted access by user level, which is equipped with inconsistency detection filters, and which affords data traceability until the database is no longer needed.

Data access: All the physicians and clinical researchers involved in the study, the Ethics Committee, and the relevant health authorities will have access to the data.

### Sample size

Sample size calculations will be performed using the statistical program Ene 2.0®. The main variable will be the existence of differences between CXR and LUS in patients with community pneumonia and nosocomial pneumonia. H1 will be considered as the existence of differences between LUS and CXR. An 80% power will be required to detect differences in the contrast of the null hypothesis H0: p1 = p2, using a bilateral X^2^ test for two independent samples. If we consider a significance level of 5%, it will be necessary to include 63 units in the control group and 63 units in the experimental group. A total of 126 patients will be included for community pneumonia. Twenty-eight patients per group will be included for nosocomial pneumonia; therefore, there will be 56 patients in total for this kind of pneumonia. After 12 months of recruitment, a preliminary analysis will be carried out to guarantee the safety of the patients. Respiratory infection represents around 30–70% of the PICU admissions, depending on the season. There will be an estimated 200–300 recruitable patients per year, so it is expected that the calculated sample size will be attainable.

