## Background

Pneumonia is responsible for more than 2 million child deaths around the world; it is the leading cause of childhood morbidity and mortality [1]. Moreover, severe lower respiratory infection is the most common cause of admission to paediatric intensive care units (PICUs) [2]. Around 60–70% of these have a viral etiology [3]. For physicians, it is important to differentiate between viral and bacterial infection because each entails a different therapeutic approach (whether antibiotics are indicated and the treatment duration), a different prognosis in the short and long term, and requires a different hospital isolation policy [4, 5]. It is challenging to rule whether a case of pneumonia is viral or bacterial in origin [6–8]. Clinical symptoms are similar and although conventional chest radiographs (CXR) have traditionally been considered the best diagnostic option [9], the specificity of CXR for determining bacterial etology remains low. Chest computed tomography may detect smaller pulmonary consolidations not visible via CXR, but it cannot be routinely performed on critically ill patients due to cost, exposure to radiation, and transportation risk [9]. Therefore, there is a need to have an examination tool that can be used at the patient’s bedside and which is easily reproducible to help detect lung consolidations. LUS has recently emerged as a radiation-free technique; it is non-invasive, with a high interobserver [10] agreement for lung pathologies such as consolidation [11], pleural effusion [12], interstitial syndrome [13], and pneumothorax [14]. To determine the etiology, conventional microbiology tests such as blood culture, pleural aspiration, and bronchoalveolar lavage are usual practices, but some of these are invasive, may not detect all etiologies [15], and the results may not be immediate.

Besides this, the use of biomarkers such as procalcitonin (PCT) has become more widespread during the past 10 years, helping clinicians diagnose bacterial etiology, especially in patients who have only had a fever for a few hours or those admitted to intensive care units [16–20]. The use of PCT has allowed for a decrease in antibiotic prescription [21, 22], even in nosocomial and community pneumonia [23, 24]. Despite its role in the diagnosis of pneumonia, PCT values without any other tests may not be a complete diagnostic biomarker for pneumonia.

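### The 63 per group and 80% power are tied to no named primary outcome; if they are meant for sensitivity and specificity, 63 is not the denominator and both cannot have that power

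*Protocol article*

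**What the plan says.** All places are in the protocol article.

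- **Outcomes.** The protocol counts as an improvement if fewer antibiotics are prescribed and if days on antibiotics fall. It then adds: "Another primary outcome will be the increase in the sensitivity and specificity when diagnosing bacterial pneumonia using LUS".
- **Sample size.** "The main variable will be the existence of differences between CXR and LUS in patients with community pneumonia and nosocomial pneumonia". The alternative is put in nearly the same terms: "H1 will be considered as the existence of differences between LUS and CXR". The power statement is "An 80% power will be required to detect differences in the contrast of the null hypothesis H0: p1 = p2", tested "using a bilateral X^2^ test for two independent samples". At 5% significance, "it will be necessary to include 63 units in the control group and 63 units in the experimental group", which is 126 children with community pneumonia. For nosocomial pneumonia the same paragraph gives 28 per group, 56 in all, without separate inputs.
- **Inclusion and exclusion criteria.** Children enter on suspicion of pneumonia, so an arm can hold both bacterial and non-bacterial cases.
- **Background.** Of severe lower respiratory infections admitted to paediatric intensive care: "Around 60–70% of these have a viral etiology".

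**The concern.** The variable that carries the power calculation restates the alternative hypothesis. It does not say what is recorded for each child, so p1 and p2 are proportions of something unnamed, and the reader cannot tell which primary outcome has 80% power. Days on antibiotics cannot be that outcome, because it is not a proportion. The wording, a difference between two imaging methods, points most naturally to the accuracy comparison. On that reading all 63 children are counted where only some of them contribute.

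At stake is how the accuracy result will be read. A non-significant difference in sensitivity from a trial described as having 80% power invites the conclusion that LUS and CXR perform alike. If the comparison rests on a fraction of each arm, that conclusion is not warranted.

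**Working it through.** **Inputs.** From Sample size: two-sided 5%, 80% power, chi-square for two independent samples, 1:1 allocation, 63 and 28 per group. Assumed here: the pair 70% v 90%, and a bacterial share of 30–40%. The share is the complement of the 60–70% viral figure in Background, used as a proxy.

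**1. Can 63 be reproduced?** Not uniquely, since p1 and p2 are not given. With p̄ = (p1 + p2)/2, the usual formula is

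n = [1.96·√(2p̄(1−p̄)) + 0.8416·√(p1(1−p1) + p2(1−p2))]² / (p1−p2)².

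For 70% v 90%: [1.96·√0.32 + 0.8416·√0.30]² / 0.04 = (1.1087 + 0.4610)² / 0.04 = 61.6, so 62 per arm. Other pairs also give 62, for example 10% v 30%, 35% v 60% and 40% v 65%. So 63 corresponds to a gap of roughly 20–25 points.

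**2. What 63 and 28 detect with 80% power** (same formula, solved for p2)

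| Per arm | from 50% | from 70% |
|---|---|---|
| 63 | 74.0% | 89.8% |
| 28 | 84.4% | 97.2% |

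At 70% v 90%, 28 per arm has 47% power. The two group sizes therefore do not give the same power for the same effect.

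**3. Denominators for accuracy.** Within an arm, (children with bacterial pneumonia) + (children without) = 63. The smaller part is at most 31, whatever p1 and p2 are. At the proxy share:

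- with bacterial pneumonia: 63 × 0.30 = 18.9 and 63 × 0.40 = 25.2, so 19–25
- without: 63 × 0.60 = 37.8 and 63 × 0.70 = 44.1, so 38–44

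**4. Power on those denominators.** This is exact power of the uncorrected chi-square test: binomial probabilities summed over all outcomes with a two-sided p below 0.05.

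| Per arm | Meaning | 70% v 90% | 50% v 74% |
|---|---|---|---|
| 63 | all children | 82% | 81% |
| 44 | specificity, 30% bacterial | 68% | 66% |
| 38 | specificity, 40% bacterial | 61% | 58% |
| 31 | smaller part at the most even split | 52% | 51% |
| 25 | sensitivity, 40% bacterial | 45% | 45% |
| 19 | sensitivity, 30% bacterial | 34% | 36% |

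The second pair also fits 63 per arm and shows the same loss, so the pattern does not hang on one choice of effect.

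**5. Precision.** For a sensitivity of 80%, the 95% half-width is 1.96·√(0.8 × 0.2 / n): 18 points at n = 19 and 16 points at n = 25, against 10 points at n = 63.

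**6. Would pooling the two strata help?** 63 + 28 = 91 per arm. At 30–40% bacterial, 27–36 per arm count for sensitivity, and power at 70% v 90% is 45–57% by the approximate formula. This is still short of 80%.

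**The case against.** **The variable may be a primary outcome, loosely named.** A reader might infer that the stated power belongs to no outcome the trial will report. The text does not go that far. If p1 and p2 are the proportions prescribed an antibiotic in each arm, all 63 children count and 80% power is attainable. The paragraph is ambiguous and does not exclude this. What stands is that it does not say so, and that accuracy would then have no stated power of its own.

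**The power for accuracy depends on the true gap.** A reader might infer that accuracy is underpowered as a matter of fact. At 50% v 90%, 19 per arm give 82% power and 25 give 91%. Only the conditional statement is secure: at the effect that makes 63 the right number, the smaller subgroup falls well short.

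**The viral figure is background, not a design assumption.** It describes severe lower respiratory infection in intensive care. The trial enrols suspected community or nosocomial pneumonia, and its definition of community pneumonia includes raised inflammatory markers, so the bacterial share may differ. This stands, and the 19–25 are illustrative. The limit of 31 does not depend on it.

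**80% is not expressly claimed for the 28.** Power and significance level are stated before the 63, and the 28 follow without either. A different size for a different population is not a contradiction. The point is only that the paragraph must not be read as giving both strata the same power for the same effect.

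**Missing p1 and p2 may be condensation.** An article may leave them to the full protocol, so their absence is not the finding. No values would let sensitivity and specificity each have 63 per arm.

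**A paired comparison would change the power.** Comparing LUS and CXR within child could do so, but the test named is for independent samples.

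A reader might also infer an inflated error rate from several primary outcomes in two populations. The article does not say that each is tested separately in each population, and its wording allows joint criteria. No such claim is made here.

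**Conclusion.** The point holds in this form: the sample-size paragraph does not tie its 63 per group and 80% power to a named primary outcome, cannot cover days on antibiotics, and uses the wrong denominator if accuracy is meant. That both sensitivity and specificity cannot have 80% power at the sizing effect follows from the split of each arm alone. It assumes only that arms contain children with and without bacterial pneumonia and that the comparison is between independent groups, as stated.

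The size is less certain. The drop from 82% to 52% rests on the assumed 70% v 90%; the 34–45% for sensitivity and 61–68% for specificity rest in addition on the proxy prevalence. The sums 126 and 56 are correct, and no arithmetic error in deriving 63 or 28 is shown or alleged.

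**What to change.** 1. State which primary outcome the 63 and the 28 per group serve, and give for each the difference it detects with 80% power. Which outcome that is remains the sponsor's choice.
2. For sensitivity and specificity, restate power or expected confidence-interval width on the expected numbers with and without bacterial pneumonia, over a stated range of prevalence.
3. Make clear that 28 per nosocomial group detect only a larger difference than 63 per group do.

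This costs a rewritten paragraph and no extra patients. The price is a less favourable stated power for accuracy: the rewrite discloses the shortfall and does not remove it. For scale, 80% power for both sensitivity and specificity at the assumed 70% v 90% would take about 62/0.30 = 207 per arm at 30% bacterial, 62/0.40 = 155 at 40%, and 62/0.50 = 124 at 50%.

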### Statistical analysis

Using the “Random” function of the MS-Excel XP® program, a binary series of random numbers will be generated, according to the procedure described by Friedman [34]. This procedure creates the sequence by means of balanced block sampling to ensure a similar number of patients in each group. The series of numbers will be in the possession of the PICU’s head researcher. Depending on that number, each patient will be assigned to one group or the other. If a patient is randomized but does not complete the treatment, their data will not be analysed, and their random number will not be reused.

The categorical variables will be compared using the Chi-square test. The quantitative analysis will be compared using Student’s t-test or the Mann-Whitney U test, depending on whether the sample follows a normal distribution or not. A multivariate logistic regression analysis will be performed on those variables with statistical significance or a clear tendency in the univariate analysis to detect which factors represent a protective factor or not, in terms of quality. The analysis of the interobserver agreement will be performed using Cronbach’s alpha. A *p* < 0.05 will be considered significant. The statistical program SPPS® 20.0 will be used.

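### The number to enrol equals the number calculated for 80% power, yet the plan drops randomised patients from analysis; the 80% holds only with no removals unless 63 per group means analysed patients

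*Protocol article*

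**What the plan says.** The Sample size section of the protocol article sets the target as follows: "An 80% power will be required to detect differences in the contrast of the null hypothesis". The test is described as "using a bilateral X^2^ test for two independent samples", with a 5% significance level. From this it concludes: "it will be necessary to include 63 units in the control group and 63 units in the experimental group. A total of 126 patients will" [...]; the total of 126 is the one to enter for community pneumonia. For nosocomial pneumonia it gives 28 per group and 56 in total. It mentions no allowance for losses.

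Two other sections take patients out after they have entered. Under Inclusion and exclusion criteria: "Patients withdrawing or with loss of protocol adherence will be excluded from the study". The withdrawal criteria listed there are breach of the protocol, parents withdrawing consent, and death. Under Statistical analysis, for a randomised patient who does not finish treatment: "their data will not be analysed, and their random number will not be reused". Neither section says that such patients are replaced.

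**The concern.** A power calculation gives the number of patients needed in the analysis. Here that number is also the number to be entered, while the same article provides for removing some of those entered. Followed as written, the analysed groups fall below 63 as soon as one patient is removed from each, and the stated power no longer describes the analysis.

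What is at stake is how a null result would be read. A non-significant comparison of ultrasound with X-ray would be presented as coming from a trial with 80% power, when the analysed groups gave somewhat less. This is a point about N and power only. The bias that can follow from excluding randomised patients is a separate matter.

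**Working it through.** **Inputs from the article.** Two-sided test at 5%; 80% power; chi-square test of two independent proportions; 63 per group (community); 28 per group (nosocomial); equal allocation by balanced blocks.

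**Inputs not in the article.** The two proportions p1 and p2: the alternative is given only as "H1 will be considered as the existence of differences between LUS and CXR". The loss rate d is also absent, so it is an assumption here, shown as a range.

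**Step 1: the totals.** 63 + 63 = 126 and 28 + 28 = 56. The sums are right, and they show that the inflation for losses is 0%.

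**Step 2: the plan's own figure.** Without p1 and p2, 63 per group cannot be reproduced. It is compatible with many pairs, for example 0.20 v 0.43, 0.50 v 0.74 or 0.70 v 0.90. The check therefore takes as given that 63 per group yields 80%, and asks what follows.

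**Step 3: the formula.** With n per group, pooled variance under the null and p̄ = (p1 + p2)/2,

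power = Φ{ [ |p1 − p2|·√n − 1.96·√(2p̄(1 − p̄)) ] / √(p1(1 − p1) + p2(1 − p2)) }.

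Worked for 0.50 v 0.74:

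- √(2 × 0.62 × 0.38) = 0.6864, and 1.96 × 0.6864 = 1.3454.
- √(0.25 + 0.1924) = 0.6651.
- n = 63: (0.24 × 7.937 − 1.3454)/0.6651 = 0.841, so power is 80.0%.
- n = 63 × 0.90 = 56.7: (0.24 × 7.530 − 1.3454)/0.6651 = 0.694, so power is 75.6%.
- n = 63 × 0.80 = 50.4: (0.24 × 7.099 − 1.3454)/0.6651 = 0.539, so power is 70.5%.

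**Step 4: does the unknown pair matter?** No. Since 2p̄(1 − p̄) = p1(1 − p1) + p2(1 − p2) + (p1 − p2)²/2, the formula reduces to Φ{ r√n − 1.96·√(1 + r²/2) }, where r is |p1 − p2| divided by √(p1(1 − p1) + p2(1 − p2)). Fixing 80% at 63 fixes r, whatever the pair. Solving numerically for p1 from 0.05 to 0.85 gave the same power to three decimals each time.

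**Step 5: results over the assumed range of loss.**

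| Assumed loss | Power, if 63 gives 80% | Power, if 28 also gives 80% |
|---|---|---|
| 5% | 77.9% | 77.8% |
| 10% | 75.6% | 75.5% |
| 15% | 73.2% | 73.0% |
| 20% | 70.5% | 70.2% |

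Rounding down to whole patients changes little for the larger cohort: 59, 56, 53 and 50 analysed per group give 77.3%, 75.1%, 72.7% and 70.2%.

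**Step 6: numbers to enter if 63 and 28 are to be analysed.** Use n/(1 − d), rounded up.

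| Assumed loss | Per group (community, nosocomial) | Total |
|---|---|---|
| 5% | 67, 30 | 134 + 60 = 194 |
| 10% | 70, 32 | 140 + 64 = 204 |
| 15% | 75, 33 | 150 + 66 = 216 |
| 20% | 79, 35 | 158 + 70 = 228 |

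The plan has 126 + 56 = 182.

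**The case against.** The best reply is that 126 may mean the patients who remain. If a removed patient is excluded from the study, that patient might not count as included. The rule on random numbers bars reusing a number; it does not bar recruiting another patient under a new one. With 200 to 300 patients a year expected to be available, against 182 planned, recruiting until 63 and 28 are analysable looks feasible. A condensed article might also leave a replacement rule to the full protocol.

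This stands in part. The text does not rule replacement out, so a reader should not infer that the analysed number is certain to fall short. But nothing says that 63 and 28 are analysed patients or that losses are made up, and the article itself fixes the number to enter, the power and the removal rules. What it states on these three does not fit together without a clarification.

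Other stronger readings also go too far. The removal rules overlap (loss of adherence largely repeats breach of protocol), so counting them as many separate sources of loss would exaggerate. Nothing in the article indicates a loss of 10% or 20%; at 5% the cost is only about 2 points. The article does not explicitly tie the 28 per group to 80% power, so it cannot be said outright that power is overstated in the nosocomial cohort. And there is no error of addition.

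**Conclusion.** The point holds as an inconsistency between the number to be entered and the rules on who is analysed. Read as written, the stated 80% requires that no randomised patient be removed. The direction is certain if removals occur without replacement; the size is not known, because it depends on a loss rate the article does not give. On the assumption that 63 per group gives 80%, the shortfall runs from about 2 points at 5% loss to about 9 to 10 points at 20%. For 28 per group the same holds only if that number was also set for 80%. A reader might infer that the trial is seriously underpowered; the article does not support that, since neither the loss rate nor the underlying effect is stated and replacement remains possible.

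**What to change.** In the Sample size section, state whether 63 and 28 per group are randomised or analysed patients, and whether 28 was also set for 80% power.

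- If they are randomised patients, restate the power at the number expected to be analysed, using the sponsor's own assumption about losses.
- If they are analysed patients, say so and replace 126 and 56 with the totals to be entered, that is 63/(1 − d) and 28/(1 − d) per group for the sponsor's d, or state that removed patients are replaced under new numbers.

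The first option changes wording only and makes the stated power slightly less favourable. The second raises the number to recruit; the table of totals above shows by how much. Neither cures the separate bias from excluding patients after randomisation, which a larger N does not remove.
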